First, the research team met with the subdistrict head and village leaders in the 2 selected subdistricts designated as the experimental areas. After obtaining their approval, the research team recorded a campaign message delivered by each subdistrict leader. The campaign content, developed by experts in malaria-related behavior, mathematical modeling, and rural development, included the main symptoms of malaria, prevention strategies, and the appropriate treatment-seeking behavior for suspected malaria cases. During the campaign, the subdistrict head occasionally emphasized key points in the local language to improve comprehension. The recorded message was then combined with a locally popular song to enhance engagement. The final recording was 15 minutes long. Second, 6 health promotion staff members from Baing and Mahu Public Health Centers were selected as RAs to play the recording. The recording was broadcast using loudspeakers to ensure wide community outreach. Third, the RAs played the recorded message once per week for 20 weeks in the 13 intervention villages. The intervention started in the fourth week of August 2024 and concluded in the second week of January 2025. In each selected village, the intervention was conducted in 4 different locations per week to ensure that all community members were reached. The principal investigator maintained weekly communication with the RAs to ensure that the intervention was being conducted properly. Over the 20-week intervention period, the research team monitored implementation by visiting the experimental villages once a month for 5 months.

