### Outcome Variables

The study considers 10 potential outcomes variables, with the first 7 serving as the primary outcomes of the intervention, while the remaining 3 represent secondary findings. The first primary outcome of the study is improvement in the malaria awareness index among rural communities. If the malaria awareness index after the intervention is higher than that before the intervention, it indicates that the health education campaign effectively enhanced malaria awareness. This index will be assessed based on 12 questions covering general knowledge of malaria, treatment-seeking behavior, and knowledge of malaria prevention measures, following the methodology of a previous study [39]. Each correct response will be assigned a score of 1, while incorrect answers will receive a score of 0, with a total possible score of 12. Participants’ knowledge level will be categorized based on their accuracy rate: 0% (zero awareness), 1% to 59% (poor awareness), 60% to 79% (good awareness), and at least 80% (excellent awareness). Those classified as having excellent or good awareness will be considered aware of malaria, while participants in the other categories will be classified as unaware of malaria [39,70]. The malaria awareness index will be calculated before and after the intervention in both the intervention and control groups to evaluate the effectiveness of the health education campaign.

The second outcome variable in this study is improvement in AMTSB. This improvement will be demonstrated if the proportion of rural adults exhibiting AMTSB after the intervention is higher than before the intervention. AMTSB is defined as seeking malaria treatment at professional health facilities within 24 hours of experiencing malaria symptoms [41]. The proportion of rural adults engaging in AMTSB will be calculated both before and after the intervention in both the intervention and control groups. This assessment will be based on the 3 key questions from the malaria treatment-seeking behavior section of the questionnaire.

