The seventh outcome variable in this study is variation in access to basic drinking water and its associated factors among rural communities in ENT Province, Indonesia. Household access to basic drinking water is defined based on the WHO Joint Monitoring Program guidelines, which classify water sources into 4 categories: no service, unimproved, limited, and basic [75]. To analyze this variable, a dichotomous classification will be used, where households will be categorized as either having access to an improved drinking water source (Yes=1) or lacking access to an improved drinking water source (No=0). This classification will help determine disparities in access to safe drinking water and identify key factors influencing these differences.

The secondary outcomes of this study are derived from the analysis of patient medical records from 4 selected health centers, along with additional data from the Department of Health, East Sumba District. The eighth outcome variable focuses on the monthly number of malaria cases recorded over the past 10 years, from 2013 to 2023. By integrating data from both health centers and the Meteorological Agency of East Sumba, this study aims to explore the impact of climatic variables on malaria case fluctuations in this region, following the methodology of a previous study [76]. This analysis will provide valuable insights into seasonal and long-term trends in malaria transmission, which could help inform future malaria prevention and control strategies.

The ninth outcome variable in this study examines the demographic variations in malaria prevalence among communities residing in hilly and coastal areas over the past 10 years (2013-2023). Among the 4 selected health centers, Baing and Nggongi Public Health centers are located in coastal areas, whereas Mahu and Kananggar Public Health Centers are situated in hilly regions. Given that vector distribution and species composition may vary between different geographic settings [77], previous studies in Indonesia have reported significant differences in malaria prevalence between coastal and hilly areas [78]. By analyzing malaria case records from these health centers, this study aims to assess regional disparities in malaria burden and determine how demographic and environmental factors contribute to these differences. This information may help tailor malaria prevention and control efforts to the specific needs of different geographic regions.

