### Statistical Analysis

All statistical analyses will be conducted using SPSS version 27 (IBM Corp), and *P* values <.05 will be considered statistically significant.

For the first outcome variable, descriptive statistics will be used to summarize participants’ sociodemographic characteristics and environmental variables including gender, age group, SES, education level, family size, distance to the nearest health facilities, village accessibility, and household location. A chi-square test will be applied within each study group (intervention and control) to evaluate the association of basic malaria understanding, basic malaria knowledge, the level of malaria knowledge, and the level of malaria awareness before and after the intervention. Unpaired sample *t* tests will be used to investigate the statistical differences. Comparisons will be performed within groups (pre- and postintervention) and between groups to determine the impact of the intervention [61]. Furthermore, a binary logistic regression model will be used to identify the potential factors associated with malaria awareness in both the intervention and control groups [39].

For the second outcome variables, descriptive statistics will be used to summarize participants’ sociodemographic and environmental characteristics including gender, age group, SES, education level, family size, distance to the nearest health facilities, access to village, and household location for both study groups. A chi-square test will be used to evaluate the association between AMTSB and the sociodemographic and environmental characteristics of participants. Unpaired samples *t* tests will be used to assess the statistical differences. Comparisons will be conducted within and between groups for both pre- and postintervention periods. Moreover, binary logistic regression analysis will be used to identify predictors associated with AMTSB among participants in both study groups [41]. Only predictors that demonstrate statistically significant differences (*P*<.05) will be retained in the final model.

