For the third variable response, participants’ sociodemographic characteristics and environmental variables in each group will be reported using descriptive statistics. The association between a good level of MPMK with predictors will be investigated using a chi-square test. Unpaired samples *t* tests will be used to investigate the statistical differences. Comparisons will be conducted within and between groups for both pre- and post-intervention periods. Furthermore, binary logistic regression analysis will be performed to identify key risk factors influencing MPMK [44,81] among rural communities in both study groups.

For the fourth outcome variable, descriptive statistics will be used to summarize participants’ sociodemographic characteristics and environmental variables based on the awareness that malaria can be prevented. Associations between bed net use and its predictors will be examined using a chi-square test. Binary logistic regression analysis will then be conducted to identify the primary risk factors associated with bed net use during the dry season among rural communities [71].

For the fifth outcome variable, participants’ sociodemographic characteristics, environmental variables, and malaria-related behavioral aspects in both the intervention and control groups will be analyzed. Data will be presented as proportions for each season (dry and wet seasons) to examine the seasonal variations in malaria prevention behaviors. The associations between bed net use and its predictors will be evaluated using a chi-square test for each season. The main risk factors for bed net use during the dry and wet seasons will be investigated using binary logistic regression analysis. The adjusted odds ratio will be used to quantify the strength of the associations between bed net use and its predictors in each season [71,72].

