For the sixth outcome variable, participants’ sociodemographic characteristics, environmental variables, and behavioral aspects of malaria in each group will be reported using descriptive statistics. The association between a good level of MPMP and its predictors will be investigated using chi-square tests. Unpaired samples *t* tests will be used to investigate the statistical differences. Comparations will be performed within and between groups for both pre- and postintervention periods. Moreover, binary logistic regression analysis will be performed to identify the primary risk factors influencing MPMP [73,74] among rural communities in both study groups.

For the seventh outcome variables, descriptive statistics will be used to summarize participants’ sociodemographic characteristics, environmental variables, and malaria-related behaviors based on their source of drinking water. The associations between access to improved drinking water and its predictors will be assessed using chi-square tests. Furthermore, a binary logistic regression model will be used to determine predictors influencing access to improved drinking water [75].

For the eighth outcome variable, descriptive analyses of climatic factors across different subdistricts will be performed. Data will be aggregated at the subdistrict level, and statistical estimates will be generated for each variable. Specifically, the total number of malaria cases and the average malaria incidence will be computed. Climatic variables, including maximum, minimum, and mean temperature values, will be calculated. Moreover, data from all 22 subdistricts will be analyzed, focusing on malaria cases and climatic parameters, including maximum, minimum, and average temperature values. To depict the seasonal dynamics, seasonal variations in climatic parameters and malaria cases will be plotted, covering the 2 main seasons. A time series for both predictor and outcome variables will be plotted to deliver an overall perspective. A map of malaria cases will be generated. Scatterplots will be developed to illustrate relationships between malaria cases and predictor variables, following the methods of a previous study [76].

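### Seven outcomes share primary status at an unadjusted .05; two cannot show a campaign effect as planned, and the four with stated group comparisons carry a familywise error of about 18.5% if independent

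*Protocol article*

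**What the plan says.** The Outcome Variables section gives the first seven of ten outcomes equal rank: "The study considers 10 potential outcomes variables, with the first 7 serving as the primary outcomes of the intervention". In order, they are the malaria awareness index, AMTSB, MPMK, dry-season bed net use, seasonal variation in bed net use, MPMP, and drinking water. The last is introduced as follows: "The seventh outcome variable in this study is variation in access to basic drinking water and its associated factors among rural communities".

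The Statistical Analysis section opens with one rule for all analyses: P "values <.05 will be considered statistically significant". No outcome leads, and no ordering, alpha split or adjustment is given.

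The planned analyses differ in kind:

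- **Awareness:** "Comparisons will be performed within groups (pre- and postintervention) and between groups to determine the impact of the intervention". AMTSB, MPMK and MPMP have similar text.
- **Dry-season net use:** "Binary logistic regression analysis will then be conducted to identify the primary risk factors associated with bed net use during the dry season".
- **Drinking water:** "a binary logistic regression model will be used to determine predictors influencing access to improved drinking water".

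Under Phase III, the recorded campaign message "included the main symptoms of malaria, prevention strategies, and the appropriate treatment-seeking behavior for suspected malaria cases".

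**The concern.** A primary outcome of an intervention should be something the intervention is meant to change, and it should have a planned test of that change. Two of the seven do not meet this description. The others share one threshold with nothing to say which result decides whether the campaign worked.

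Within a single outcome the deciding comparison is also open. For AMTSB, MPMK and MPMP, the Outcome Variables section treats a higher proportion after the campaign than before as showing improvement. The Statistical Analysis section then lists both within-group and between-group comparisons and names both chi-square and t tests.

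At stake is what may be claimed. Several papers are planned, and as the plan stands any significant result among the seven can be reported as a primary success of the campaign.

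**Working it through.** **1. Can each of the seven show a campaign effect as planned?**

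| Outcome | In the four objectives? | Stated analysis |
|---|---|---|
| 1 Awareness | Yes | Within- and between-group comparisons |
| 2 AMTSB | Yes | Within- and between-group comparisons |
| 3 MPMK | Yes | Within- and between-group comparisons |
| 4 Dry-season net use | Net use in general is | Chi-square with predictors and a risk-factor regression; no group comparison |
| 5 Seasonal net use | Net use in general is | Seasonal difference assessed in each group, with predictors by season; no between-group test |
| 6 MPMP | Yes | Within- and between-group comparisons |
| 7 Drinking water | No | Chi-square with predictors and a logistic predictor model; no group comparison |

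*Outcome 7.* The objectives (Abstract and Introduction) and the campaign content (Phase III) do not mention water. The Independent Variables section uses access to drinking water sources as an input to the SES index, that is, as a household characteristic.

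*Outcome 4.* It is measured by whether the respondent slept under a net the night before the survey. The Results section dates the baseline survey to August-September 2024. Phase IV dates the follow-up from the third week of January to the second week of February 2025. Outcome Variables puts the start of the campaign, in late August, in the dry season and its end, in the second week of January, in the wet season. Previous-night use in the dry season therefore appears to come from the baseline survey. This is an inference from the dates; the article does not say it.

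Four outcomes (1, 2, 3, 6) thus have a stated comparison that could be read as a campaign effect. Outcome 5 is a possible fifth.

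**2. Familywise error.** Inputs: .05 per test, taken as two-sided because the article does not say; one test per outcome; all null hypotheses true; each test holding its own 5% level.

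Formula for k independent tests: 1 − 0.95^k.

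- k = 4: 1 − 0.95^4 = 0.185
- k = 5: 1 − 0.95^5 = 0.226

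The upper bound under any dependence is k × 0.05, which is 0.20 and 0.25.

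Simulation of equally correlated z-tests (400,000 draws; the correlations are assumptions):

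| Correlation | 4 tests | 5 tests |
|---|---|---|
| 0 | 18.5% | 22.6% |
| 0.3 | 17.4% | 20.8% |
| 0.5 | 15.7% | 18.3% |
| 0.8 | 11.3% | 12.7% |

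**3. More than one test per outcome.** If each of the four outcomes had four comparisons (an assumed count), there would be 16 tests, and independence would give 1 − 0.95^16 = 0.560. Comparisons on the same outcome are not independent, and a between-group comparison at baseline is not a test of effect. This figure shows direction only.

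**4. Which outcome underlies the sample size?** The article's figure reproduces: 1.96² × 0.488 × 0.512 / 0.05² = 383.9, rounded to 384; 384 × 2 = 768; 768 × 1.15 = 883.2, rounded up to 884. The 48.8% is the prevalence of malaria awareness, so awareness is the only outcome that enters. The formula is one of precision and no power is stated, so no documented power figure depends on this point.

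**The case against.** **Separate questions.** The four objectives ask different things, and whether separate questions need joint error control is debated. Multiplicity rules are also often left to an analysis plan that is not shown here. The first part has some force: a single primary outcome is one acceptable solution among several. The second has less, because the article itself fixes both the seven primary outcomes and the common threshold, and a later plan would have to depart from it.

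**A labelling slip.** The Abstract confines improvement to awareness, AMTSB, MPMK and MPMP, and the drinking-water analysis is plainly associational. That is fair. The fault with outcome 7 is its label, and it adds no false claim of campaign success.

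**Weak basis for choosing awareness.** The sample size section refers to study outcomes in the plural, and awareness supplies only p, which at 48.8% is close to the value of maximum variance. This stands. Awareness is a reasonable choice because it is listed first and supplies p; no power calculation supports it.

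**Stronger readings a reader might infer.**

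- *Seven primary tests give 1 − 0.95^7 = 30.2%, so a false positive is likely.* This counts outcomes 4 and 7, whose stated analyses do not test the campaign. It also assumes independence, although the awareness index covers treatment seeking and prevention knowledge and so overlaps with AMTSB and MPMK. Even 30.2% is below one half.
- *One paper per outcome.* The article says only that multiple papers are being drafted.
- *Outcome 4 is defined as baseline-only.* The article does not say this; it rests on the survey dates.
- *Clustering makes the figures worse.* That is a separate issue and is not counted here.

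**Conclusion.** The point holds. The plan gives seven outcomes equal primary status at an unadjusted .05. Drinking-water access and dry-season net use cannot show a campaign effect with the analyses stated; for the second, the timing argument is an inference.

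For the four outcomes with stated group comparisons, the chance of at least one false positive is about 18.5% instead of 5% if the tests are independent, and about 11% to 17% over assumed correlations of 0.8 to 0.3. Adding outcome 5 gives 22.6% if independent. These figures assume one test per outcome, all nulls true, and each test holding its level. They rise if several comparisons per outcome are counted. The documents do not support saying that a false positive is more likely than not.

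**What to change.** 1. Name the malaria awareness index as the single primary outcome, tested by one between-arm difference in change at .05. Respondents may differ between the two surveys (Phase IV), so the change is that of the group, not of the individual.
2. Make AMTSB, MPMK, MPMP and the pre-to-post change in net use the night before the survey, each compared between arms, secondary outcomes with Holm adjustment. This also gives the net-use objective a stated test of effect.
3. Reclassify dry-season net use and drinking-water access as descriptive or associational.
4. Apply the same hierarchy in every paper. Post-test collection was due to end in February 2025, with final analysis from March 2025, so state openly if the hierarchy was set after analysis began.

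No new data are needed. The cost is power for the secondaries: Holm over four starts at .05/4 = .0125.

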**Methods:**

This study used a cluster-assigned quasi-experimental design with pretest and posttest assessments in control and intervention groups. The control group, consisting of 12 villages, received malaria education integrated into routine health services provided by local health centers. The intervention group, comprising 13 villages, received the same education as the control group, in addition to a malaria campaign conducted once a week for 20 weeks. Before and after the campaign, a household survey was conducted to assess behavioral aspects of malaria, including general knowledge of malaria, AMTSB, and malaria prevention measures knowledge and practice. Improvement in the malaria awareness index, AMTSB, good level of malaria prevention measure knowledge, and good level of malaria prevention measure practice will be determined based on the difference scores for each index before and after the intervention in both groups. The chi-square test will be used to assess score differences. Binary logistic regression analysis will be conducted to identify key risk factors associated with changes in each index.

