#### Phase IV (Evaluation Stage)

At this stage, the research team conducted a household survey in both the intervention and control groups using the same questionnaire that was administered during the baseline phase of the study. The final data collection was done from the third week of January 2025 to the second week of February 2025. Since the research aims to assess the impact of the intervention on all rural adults, participants surveyed before and after the intervention may differ, depending on respondent availability during the data collection period.

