The third outcome variable in this study is improvement in good MPMK. This improvement will be demonstrated if the percentage of the rural population with good MPMK after the intervention is higher than before the intervention. A good level of MPMK is defined as the ability to correctly answer at least one-half of the total questions in the MPMK section, as indicated in previous studies [41,59]. The level of MPMK will be assessed before and after the intervention in both the intervention and control groups.

The fourth outcome variable is the use of bed nets during the dry season in high malaria-endemic settings. Community behaviors regarding bed net use may exhibit seasonal variations, as individuals may adjust their practices depending on weather conditions [71]. This outcome will be assessed based on the participants’ self-reported responses to a survey question asking whether they slept under a bed net the night before the survey.

The fifth outcome variable in this study is the variation in the use of a bed net in the dry and wet seasons. The literature indicates that bed net use might fluctuate based on seasonal weather conditions, as individuals adapt their malaria prevention behaviors accordingly [71,72]. This malaria awareness campaign began at the end of August 2024, during the dry season, and concluded in the second week of January 2025, which corresponds to the wet season in the study area. The study will examine seasonal differences in bed net use by analyzing responses to 4 key questions from the malaria prevention practice section of the questionnaire. The disparity in bed net use between dry and wet seasons will be assessed for both the intervention and control groups.

The sixth outcome variable in this study is improvement in good MPMP. Improvement will be demonstrated if the percentage of the rural population practicing good MPMP after the intervention is higher than before the intervention. A good level of MPMP is defined as the ability to correctly answer at least one-half of the total questions in the MPMP section, as indicated in a previous study [73,74].

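### Improvement is defined as a rise from before to after, and no planned test compares the change between arms, so a shift common to both arms can be credited to the campaign

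*Protocol article*

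**What the plan says.** Under Outcome Variables, the article states that a campaign effect on awareness is indicated if the index "after the intervention is higher than that before the intervention, it indicates that the health education campaign effectively enhanced malaria awareness". The definitions for three other primary outcomes follow the same pattern:

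- AMTSB: "This improvement will be demonstrated if the proportion of rural adults exhibiting AMTSB after the intervention is higher than before the intervention".
- MPMK: improvement is shown if "the percentage of the rural population with good MPMK after the intervention is higher than before the intervention".
- MPMP: improvement is shown if "the percentage of the rural population practicing good MPMP after the intervention is higher than before the intervention".

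None of these sentences mentions the control group's change, although the outcomes are to be measured at both waves in both arms.

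Under Statistical Analysis, the awareness outcome gets a chi-square test inside each arm, unpaired t tests, and this: "Comparisons will be performed within groups (pre- and postintervention) and between groups to determine the impact of the intervention". Within-arm and between-arm comparisons for both periods are also listed for AMTSB, MPMK and MPMP. The logistic models look for factors associated with each outcome. The abstract says that improvement "will be determined based on the difference scores for each index before and after the intervention in both groups". The section on the evaluation stage adds that "participants surveyed before and after the intervention may differ, depending on respondent availability during the data collection period".

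**The concern.** A control arm measured at both waves serves to remove whatever would have happened without the campaign. A rule that looks only at the rise from before to after does not use it for that purpose.

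The article itself describes influences that could move both arms together. The campaign began in the dry season and ended in the wet season, and the follow-up survey came after it ended. Routine malaria education continued at health centres in both arms. Season is best documented for bed net use, which the article says may vary with the weather.

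The listed comparisons do not fill the gap. Separate within-arm tests invite the conclusion that a significant rise in one arm and a non-significant one in the other is a campaign effect. A between-arm comparison after the campaign carries any baseline difference with it. That matters here because the study is quasi-experimental, with two subdistricts assigned to each arm, and its limitations paragraph concedes possible selection bias. At stake is the study's central claim: a positive conclusion could be reached with no campaign effect at all.

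**Working it through.** **Inputs from the article.** Awareness prevalence 48.8%, z = 1.96, precision 0.05, correction factor 2, buffer 15%, 442 per arm, significance at P<.05 (taken as two-sided), 894 respondents. An even split of 894 gives 447 per arm; the article does not give the split.

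**The plan's own figure.** 1.96² × 0.488 × 0.512 / 0.05² = 383.9, so 384. Then 384 × 2 = 768, and 768 × 1.15 = 883.2, so 884, or 442 per arm. The stated size reproduces. It is a precision calculation for a single prevalence and sets no target for a between-arm change.

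**Assumptions.** The article gives no size for a common shift, so 5 and 10 points are assumed. Respondents are treated as independent, both arms start at 48.8%, and there is no campaign effect.

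**Within-arm test.** With n = 442 per wave, SE = √[(p₀(1−p₀) + p₁(1−p₁))/n], and the chance of a significant rise is Φ(shift/SE − 1.96).

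- Shift 0: Φ(−1.96) = 2.5%.
- Shift 5 points: SE = √[(0.2499 + 0.2486)/442] = 0.0336; Φ(1.49 − 1.96) = 32%.
- Shift 10 points: SE = √[(0.2499 + 0.2423)/442] = 0.0334; Φ(3.00 − 1.96) = 85%.

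**Significant in intervention, not in control.** With the same shift in both arms, this has probability P(1−P):

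- 5 points: 0.319 × 0.681 = 22%.
- 10 points: 0.850 × 0.150 = 13%.
- The maximum is 25%, at P = 0.5, where the shift is about 1.96 × 0.0334 = 6.6 points.

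If the correction factor of 2 is read as a design effect (effective n = 221), a significant rise occurs 18% and 56% of the time at 5 and 10 points, and the split result 15% and 25%. Using 447 in place of 442 changes none of these by more than about half a percentage point.

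**Post-only comparison.** If both arms start equal, it favours the campaign falsely 2.5% of the time, whatever the common shift. If the intervention arm starts 5 points higher (48.8% against 53.8%, an assumption) and nothing changes, the first formula applies again: Φ(0.05/0.0336 − 1.96) = 32%.

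**Difference in change.** A common shift, or a baseline difference that stays constant, cancels from its expectation. The price is variance. With control drift of 5 points, SE = √[(2p₀(1−p₀) + p_c(1−p_c) + p_t(1−p_t))/n], where p_c = 0.538 and p_t = 0.538 + effect.

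| True difference in change | Power, n = 442 | Power, effective n = 221 |
|---|---|---|
| 5 points | 18% | 11% |
| 10 points | 57% | 32% |
| 15 points | 90% | 62% |
| 20 points | 99% | 87% |

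Power of 80% needs about 13 points at n = 442: SE = √[(0.4997 + 0.2486 + 0.2211)/442] = 0.0468, and 0.132/0.0468 − 1.96 = 0.86. At effective n = 221 it needs about 18 points. Neither figure allows for clustering at subdistrict level.

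**The case against.** The best defence is that the control arm is not ignored. The awareness paragraph ends by saying that the index is measured before and after in both arms to judge effectiveness. Between-arm comparisons at both periods are planned for all four outcomes, so a baseline imbalance would at least be visible. A journal article may also leave the exact model term to a fuller plan. The first two points stand, and they are why a common shift can be credited to the campaign rather than will be. The third does not rescue a decision rule that the article itself states.

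Several stronger readings are tempting but are not supported:

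- *All four rules claim campaign effectiveness.* Only the awareness sentence attributes the rise to the campaign. The other three define when improvement is shown.
- *The rule is met half the time by chance.* That holds only if any rise counts. The article sets P<.05, and with no shift a significant rise occurs 2.5% of the time.
- *A quarter of such trials would show a false contrast.* That is the maximum at one assumed shift, and it arises only if the planned between-arm comparison is disregarded.
- *Repeat interviewing explains a rise.* This is weakly supported, since respondents may differ between waves.
- *The abstract's difference scores are impossible.* They can be read as group-level change, although the abstract does not say that they are contrasted between arms.

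**Conclusion.** The concern holds in this form: a before-to-after rise is taken as evidence that the campaign worked for awareness, the same rise defines improvement for AMTSB, MPMK and MPMP, and no stated test compares the change in one arm with the change in the other. A shift common to both arms, or a baseline difference between non-randomised arms, can therefore be reported as a campaign effect.

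The error rates in the working illustrate the mechanism and do not forecast this study. They rest on assumed shifts, equal baselines except where stated, and independent respondents. That no between-arm test of change is stated rests on the text alone.

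The gap also reaches the objective on net use. The bed net analyses examine predictors in each season and state no contrast that separates campaign from season, yet this is where the article documents seasonality best.

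**What to change.** For outcomes 1, 2, 3 and 6, and for the bed net effect in objective 4:

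1. Replace the before-to-after sentences with a definition of the campaign effect as the between-arm difference in pre-post change. Keep within-arm changes as description.
2. Estimate it as the group-by-period term, with a 95% confidence interval, in one model per outcome over both arms and both waves. Adjust for the respondent characteristics already collected, because the people interviewed may differ between waves, and account for clustering by village.
3. State that assigning only two subdistricts per arm limits the inference, whatever the model.
4. Say that difference scores in the abstract means group-level change contrasted between arms.
5. Add a sensitivity analysis in people interviewed at both waves only if they can be linked. The article describes no linkage.

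The cost is wording and one model per outcome on data already collected; Table 1 places the final analysis between March 2025 and December 2026. Because the follow-up survey is complete, the change should be dated and reported as such. The real price is precision: in the 5-point illustration with no campaign effect, the standard error of the difference in change is about √2 times that of a within-arm change (0.0475 against 0.0336), so modest effects may not be detectable.
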